**Methods/design:**

The study is conducted as a randomised controlled trial. The complex diagnostic assessment includes the completion of a symptom diary over two consecutive cycles and a telephone interview. Eligible women are randomly assigned to either a treatment or a wait-list control group. The intervention is based on cognitive behavioural therapy principles and is provided via the internet. It consists of 14 different modules on which participants work over 8 consecutive weeks. In addition to written information, participants receive email feedback from a clinical psychologist on a weekly basis. Participants assigned to the wait-list receive the treatment after the end of the waiting period (8 weeks). The primary outcome measure is the Premenstrual Syndrome Impairment Measure. Secondary outcomes include the Premenstrual Syndrome Coping Measure, the Short-Form Social Support Questionnaire, the Questionnaire for the Assessment of Relationship Quality, and the Perceived Stress Scale. Data is collected during the premenstrual (luteal) phase at pre-treatment, post-treatment, and 6-month follow-up.

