[41] reveals the importance of new approaches for treating PMS. Our treatment is conducted as an internet-based programme. This decision was reached for the following reasons. First, an internet-based approach enables us to provide treatment for a greater number of women and can therefore reduce waiting time for patients
[42]. Second, stigma associated with seeing a psychologist and conveying sensitive information to a person can be reduced
[42, 43]. This advantage seems to be particularly important because of taboos and stigmata linked with the topics of menstruation and PMS
[44, 45], the women’s fear and experience of not being taken seriously
[38, 41, 46], and their mainly medically oriented perception of PMS
[38]. Positive effects of internet-based CBT (iCBT) in reducing impairment or symptom severity have been found for several functional syndromes or psychosomatic disorders (for example, pain, headache
[47], or tinnitus
[48]) as well as for depression
[49]. Hence, it is highly probable that an iCBT programme can equally well target the somatic symptoms and the affective symptoms that go along with PMS/PMDD.

This study aims to evaluate the efficacy of an iCBT self-help programme for reducing mental and functional impairment in women suffering from severe PMS or from PMDD and improving their coping strategies. First, we hypothesize that the treatment group receiving the iCBT will show a lower impairment than the wait-list control group. Second, we hypothesize that the treatment group improves its coping strategies in comparison to the wait-list control group.

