#### Primary outcome

**Impairment caused by premenstrual symptoms** The impairment caused by the premenstrual symptoms is measured with a self-developed questionnaire called the Premenstrual Syndrome Impairment Measure (PMS-B), based on the German Pain Coping Questionnaire
[51], the Pain Disability Index
[52] and the Self-Report Measure for the Assessment of Emotion Regulation Skills
[53]. It is currently being validated in a pilot study. It consists of two subscales (mental and functional impairment), with seven items for each. The five-point Likert scale ranges from 0 (not true at all) to 4 (absolutely true). Mean values for the subscales as well as for the whole test are calculated.

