#### Secondary outcome

**Coping with premenstrual symptoms** Coping with premenstrual symptoms is assessed by a self-developed questionnaire, the Premenstrual Syndrome Coping Measure (PMS-C). It is based on the German Pain Coping Questionnaire
[51], the German Version of the Coping Strategies Questionnaire
[54], the Self-Report Measure for the Assessment of Emotion Regulation Skills
[53], and the Brief COPE
[55]. It consists of five scales with four items each, which are replied to on a five-point scale ranging from 0 (not true at all) to 4 (absolutely true). Mean values are calculated for the subscales as well as for the total scale. This questionnaire is also being validated in a pilot study.

**Social support** The Short-Form Social Support Questionnaire
[56] is employed to measure the availability of social support. This 22-item measure consists of three subscales: emotional support, practical support, and social integration. Four additional items measure satisfaction with the social support and availability of a person of trust. Each item is rated on a five-point scale ranging from 1 (not true at all) to 5 (absolutely true). A mean value for the whole scale is calculated
[57]. A moderate to high reliability has been found in different studies
[57, 58]. A good to very good factorial validity has been demonstrated
[57].

**Quality of partnership** The quality of partnership is measured with a 25-item measure, the Questionnaire for the Assessment of Relationship Quality
[59]. It consists of six scales: fascination (three items), engagement for the relationship (five items), sexuality in the relationship (five items), perspective of the relationship regarding the future (five items), mistrust to the partner (three items), and restriction of the independency (five items). The single subscales as well as the total score can be interpreted. Good psychometric properties have been shown with Cronbach’s alpha for the subscales ranging between 0.75 and 0.94
[59]. Good to very good convergent validity was demonstrated (r = 0.59 to 0.84) by two questionnaires measuring partnership quality and partnership satisfaction and a further questionnaire measuring depressive mood
[59].

**Level of stress** The Perceived Stress Scale is used to assess the appraisal of situations in life as stressful, particularly as "unpredictable, uncontrollable, and overloaded"

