### Statistical analysis

All analyses of the outcomes will be conducted as intention-to-treat analyses. Between-group changes at post-treatment on the impairment and the use of coping strategies will be calculated by using a 2 (pre-treatment/post-treatment) × 2 (experiment group/waiting list) MANOVA. *Post hoc* comparisons will be applied if clarification of the main effects of the MANOVA is needed. Effect sizes between the groups will be calculated with Hedges’ g.

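### Impairment is the sole primary outcome, but the only stated test is one MANOVA on impairment and coping together, so a significant result need not mean that impairment fell

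*Protocol article*

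**What the plan says.** The Abstract (Methods/design) fixes the hierarchy: "The primary outcome measure is the Premenstrual Syndrome Impairment Measure". The same paragraph puts coping (PMS-C) on the lower tier: "Secondary outcomes include the Premenstrual Syndrome Coping Measure". The Assessments section repeats this split under its Primary outcome and Secondary outcome headings.

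The Background ends with two separate hypotheses: "First, we hypothesize that the treatment group receiving the iCBT will show a lower impairment than the wait-list control group", and then "Second, we hypothesize that the treatment group improves its coping strategies in comparison to the wait-list control group".

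The Statistical analysis section gives one inferential procedure for both: "Between-group changes at post-treatment on the impairment and the use of coping strategies will be calculated". The method it names is a single MANOVA with time and group as its two factors, each at two levels. It adds that post hoc comparisons will be made if the MANOVA's main effects need clarifying, and that between-group effect sizes will be reported as Hedges' g. It does not say that impairment is tested alone, is tested first, or decides the trial.

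Sample size and power calculations gives f = 0.25, α = 0.05 and 80% power, mentions a conservative retest reliability without a value, and sets N = 128 for a 2 × 2 MANOVA.

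**The concern.** The stated test does not match the stated primary outcome. A two-outcome MANOVA tests the joint null that the groups differ on neither impairment nor coping. Rejecting it says that at least one of the two, or some combination of them, differs. It does not say which.

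This matters here because the programme teaches coping directly: relaxation, restructuring of cognitions and new appraisals all appear in Table 1. A change in coping with little change in impairment is therefore a realistic outcome. If the joint test were then reported as the result of the trial, the answer to the first hypothesis would rest on the secondary outcome.

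The follow-up comparisons do not settle this as worded. They are conditional, they name no outcome and no alpha, and they refer to main effects. In a time × group layout the treatment effect is the group × time interaction, not a main effect.

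**Working it through.** **Inputs from the article.** f = 0.25, α = 0.05, power 80%, N = 128. For two equal groups d = 2f = 0.5.

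**Assumptions.** The article does not state the allocation ratio, so 1:1 (64 per arm) is assumed. It gives neither the effect on coping nor the correlation between the two outcomes. These are shown as ranges: d = 0.3, 0.5 and 0.8, and |r| = 0 to 0.6. Here d is the standardised group difference in the analysed (change) score.

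**Step 1: reproduce N = 128.** Noncentrality λ = f²N = 0.0625 × 128 = 8.
- One outcome, F(1,126): power 0.801, and 128 is the smallest even N that reaches 80%.
- Two outcomes, F(2,125), same λ: power 0.706, and 80% would need N = 158.

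The stated sample size is thus that of a test on one outcome.

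**Step 2: chance that the joint test rejects when impairment does not move.** λ = (64/2) × d²/(1 − r²) = 32d²/(1 − r²), referred to F(2,125). The sign of r does not matter.

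| Coping d | r = 0 | 0.3 | 0.5 | 0.6 |
|---|---|---|---|---|
| 0.3 | 30% | 33% | 39% | 45% |
| 0.5 | 71% | 75% | 83% | 89% |
| 0.8 | 98.5% | 99.1% | 99.8% | 99.9% |

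Example: d = 0.5, |r| = 0.5 gives λ = 32 × 0.25/0.75 = 10.67 and a rejection probability of 0.832.

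In a simulation of 20,000 trials per scenario at coping d = 0.5, the MANOVA was significant while impairment was not (p > 0.05) in 66% of trials at r = 0 and 78% at r = −0.5.

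**Step 3: require the MANOVA and then an impairment test, each at 5%.** With no impairment effect and coping d = 0.5 to 0.8, simulation finds both significant in about 5% of trials. If nothing moves, the figure is about 2.5%. Error on the impairment claim is therefore controlled.

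**Step 4: what the two-step route costs.** If only impairment moves (d = 0.5), the MANOVA is significant in 71% of trials at r = 0 and 75% at |r| = 0.3. Requiring the impairment test as well gives about 70% power over that range (simulation runs between 69% and 72%). A direct impairment test has 80.1%.

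**The case against.** Three arguments on the other side have weight.

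**A reader might infer that the plan cannot control type I error for impairment.** The documents do not support that. Post hoc comparisons are foreseen, and with only two outcomes a joint test followed by a 5% test on each is a closed procedure; step 3 confirms it. The percentages in step 2 are correct rejections of a false joint null. They become false impairment claims only if the joint result is read as an impairment result, and nowhere does the article say it will be. What remains is that the follow-up is conditional, aimed at main effects and not assigned to impairment.

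**The MANOVA may be meant as a repeated-measures analysis run once per outcome.** The label 2 × 2 counts time and group, retest reliability is a within-outcome quantity, N = 128 matches a one-outcome test, and Hedges' g is calculated per outcome. This reading is open. But the sentence names both outcomes under one MANOVA and does not say they are analysed separately, so the primary test is at best ambiguous.

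**If both outcomes move as hypothesised, the joint test loses nothing.** With d = 0.5 on both in the expected directions and a correlation of −0.3 to −0.5, its power is 88% to 83%. That is true, but a rejection would still not identify impairment.

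A reader might also see a multiplicity problem in the PMS-B scoring: "Mean values for the subscales as well as for the whole test are calculated". That sentence describes how scores are formed. It plans no separate test of each, so no inflated error rate follows from it.

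**Conclusion.** The point holds as a mismatch between the primary outcome and the only stated test. Taken literally, a significant MANOVA is not evidence that impairment fell: with no impairment effect it would occur in about 30–45%, 71–89% or at least 98.5% of trials for coping effects of 0.3, 0.5 and 0.8. These figures rest on 64 per arm and on assumed coping effects and correlations. They do not show that the trial must produce a false impairment claim, since a 5% impairment follow-up would keep that error near 5%. That route would still give up about ten points of power if impairment alone moves and the correlation is low. The sample size figure itself is sound for a one-outcome test. This is worth settling before analysis, because it determines what the headline result means.

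**What to change.** In Statistical analysis, state that the first hypothesis is decided by the between-group comparison of the PMS-B total score from t1 to t2 (group × time, or t2 adjusted for t1), tested alone at two-sided 5%. State that PMS-C is tested separately as secondary, for example in fixed sequence after PMS-B, which costs no alpha. The joint MANOVA can stay if it is labelled supportive and not the decision test.

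In Sample size and power calculations, describe N = 128 as sized for this one-outcome test (f = 0.25, α = 0.05, power 80%).

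The cost is a few sentences. No extra patients or data are needed, and Trial status reports recruitment as still ongoing at publication.

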### Sample size and power calculations

Effect sizes of the difference between an iCBT programme for PMS and a wait-list control group cannot be estimated precisely because the combination of these two approaches – CBT and internet-based interventions – for treating PMS has not yet been evaluated systematically.

First, there is currently no internet-based self-help programme for PMS. However, iCBT has been found to be effective for disorders sharing common symptoms with PMDD (for example, affective and somatic disorders)
[39]. Large effects for internet-based treatments with psychologist support for depression and anxiety disorders compared to control conditions were found in a meta-analysis
[49]. The effects found for internet-delivered treatments aimed at health problems (pain and headache) were comparable to the effects for face-to-face interventions
[47].

Second, CBT face-to-face programmes for PMS are not well evaluated and suffer from a limited methodological quality as well
[36, 39]. In one meta-analysis examining CBT for PMS
[36] the authors found medium effect sizes. Small to medium effect sizes were found in another meta-analysis comparing CBT and pharmacological interventions
[40].

By considering the different effect sizes found in the cited studies and the insufficient current state of research, we based our sample size calculation on an expected medium effect size (*f* = 0.25, α = 0.05, power 80%). The validity and retest reliability of two applied tests is evaluated in a pilot study and thus is not known yet. Therefore, we assumed a conservative retest reliability. For a 2 × 2 multivariate analysis of variance (MANOVA) the total sample size is set to *N* = 128.

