### Patient recruitment, randomization and procedure of the treatment

Participants are recruited via articles in newspapers, family doctors and gynaecologists, flyers, and different social networks.

Eligible participants undergo four assessments (see Figure 
1). In the first assessment (t0-assessment), participants fill out a retrospective screening of premenstrual symptoms
[50] according to the DSM-5 criteria
[7]. If participants fulfil the basic inclusion criteria and primary DSM-5 criteria (that is, five premenstrual symptoms including at least one affective symptom), a structured clinical interview regarding comorbid disorders is conducted via telephone. Afterwards, principally eligible participants are invited to complete a daily symptom rating during two consecutive menstrual cycles, as requested by the DSM-5 and ACOG criteria. During one of the premenstrual (luteal) phases within these two cycles, the participants fill in the pre-treatment assessment (t1-assessment) including primary (impairment of premenstrual symptoms) and secondary outcome measures (coping with premenstrual symptoms, social support, quality of partnership, level of stress). If the participants fulfil the diagnostic criteria of a severe PMS or PMDD with regard to the daily symptom rating, they are randomly assigned to either the treatment or the wait-list control group. In addition, they are randomized to one of two psychologists who will be the responsible psychologist throughout the study.

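### The pre/post by group MANOVA compares change scores; adjusting for the pre-randomisation score would be more precise at almost no cost

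*Protocol article*

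**What the plan says.** The Statistical analysis section sets out the comparison as "Between-group changes at post-treatment on the impairment and the use of coping strategies", which "will be calculated by using a 2 (pre-treatment/post-treatment) × 2 (experiment group/waiting list) MANOVA". It names no model with the baseline score as a covariate. It also does not name the group-by-time interaction as the test of interest, though a between-group difference in change can only be that interaction.

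The Sample size and power calculations section gives an "expected medium effect size (*f* = 0.25, α = 0.05, power 80" (the last figure is a percentage), and for a 2 × 2 MANOVA "the total sample size is set to *N* = 128". On the reliability of the two self-developed scales it says: "The validity and retest reliability of two applied tests is evaluated in a pilot study and thus is not known yet". It continues: "Therefore, we assumed a conservative retest reliability". It gives no value, and it does not say whether f is defined on the SD of the score or of the change.

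Under Patient recruitment, randomization and procedure of the treatment, the t1 questionnaires are completed during the two diary cycles. Women who then meet the diagnostic criteria are allocated: "they are randomly assigned to either the treatment or the wait-list control group". So t1 precedes allocation. The abstract and the Primary outcome section name the impairment measure (PMS-B) as primary. Coping (PMS-C) is secondary.

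**The concern.** A repeated-measures analysis with one pre and one post measurement subtracts the whole baseline score from the post score. That is the best use of the baseline only when the regression slope of post on pre is 1. With a lower slope, subtraction over-corrects and adds the noise of the baseline measurement. With equal SDs and r below 0.5, the change score is even less precise than the post score alone.

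The choice matters here because the outcome scales are new and their retest reliability was unknown at planning. An analysis whose precision depends on a high pre-post correlation therefore rests on a quantity the investigators did not have. ANCOVA estimates the slope from the data and does not need that guess. What is at stake is precision and power on the primary question, and less sensitivity of the realised estimate to a chance imbalance at t1.

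**Working it through.** **Inputs from the article.** f = 0.25, α = 0.05, power 80%, N = 128; two time points and two groups; t1 before randomisation.

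**Assumptions, since the article does not give them.** 1:1 allocation (64 per arm), equal pre and post SDs, no dropout, a two-sided test, and r between 0.2 and 0.7 for display.

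**Step 1: reproduce N = 128.** For two equal groups d = 2f = 0.5. A one-df F test has noncentrality λ = f²N = 0.0625 × 128 = 8 on 1 and 126 df, which gives 80.1% power. The smallest even N reaching 80% is 128, so the figure reproduces. Other conventions do not give it. A repeated-measures interaction with f in cell-SD units needs 66, 54 or 34 at r = 0, 0.2 or 0.5. A joint two-outcome test with effect size f² = 0.0625 (2 and N − 3 df) needs 158.

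**Step 2: what the interaction tests.** For each outcome the contrast is (post − pre) in the treatment group minus (post − pre) in the wait-list group, so it is a two-sample test on change. Per-participant variances in units of the score variance:
- change score: 2(1 − r)
- ANCOVA: (1 − r²) × (N − 3)/(N − 4) = (1 − r²) × 125/124, with N − 3 = 125 error df

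Before the factor 125/124 = 1.008, the ratio ANCOVA/change is (1 − r²)/[2(1 − r)] = (1 + r)/2, which is below 1 for every r below 1. With the factor, ANCOVA has the smaller standard error for r < 2 × 124/125 − 1 = 0.984.

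**Step 3: power if d = 0.5 is on the score SD.** λ is 8 divided by the variance from step 2.

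| r | λ, change | Power, change | λ, ANCOVA | Power, ANCOVA | N for 80%, change / ANCOVA |
|---|---|---|---|---|---|
| 0.2 | 8/1.6 = 5.00 | 60.2% | 8/(0.96 × 1.008) = 8.27 | 81.4% | 204 / 124 |
| 0.3 | 8/1.4 = 5.71 | 66.0% | 8/(0.91 × 1.008) = 8.72 | 83.4% | 178 / 118 |
| 0.5 | 8/1.0 = 8.00 | 80.1% | 8/(0.75 × 1.008) = 10.58 | 89.8% | 128 / 98 |
| 0.7 | 8/0.6 = 13.33 | 95.2% | 8/(0.51 × 1.008) = 15.56 | 97.5% | 78 / 68 |

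Simulation with 20,000 trials per row agrees to within about half a percentage point.

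**Step 4: power if f = 0.25 is on the change-score SD.** The planned test has λ = 8 and 80.1% power whatever r is. ANCOVA has λ = 8 × [2/(1 + r)]/1.008:
- r = 0.3: λ = 12.21, power 93.4%
- r = 0.5: λ = 10.58, power 89.8%
- r = 0.7: λ = 9.34, power 85.8%

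**Step 5: where ANCOVA could lose.** Its worst case is a true slope of exactly 1, for example baseline SD 0.8 of the post SD with r = 0.8. Its standard error is then larger by √(125/124) = 1.004, or 0.4%. If the baseline SD is instead 1.25 times the post SD, the gain is larger: at r = 0.5, 68.8% for change against 89.8%.

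**The case against.** The planned test is not wrong. Under randomisation the change-score contrast is unbiased and keeps its type I error. It also uses the baseline: at r = 0.7 it has 95% power, against about 80% for a post-only comparison. It loses to post-only only when r is below 0.5 (equal SDs). All of this stands, so the point is one of efficiency.

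A reader might infer that the trial is underpowered for its own analysis. The article does not support that. A conservative reliability is a planning input, not evidence that the true correlation is low, and no value is given. N = 128 is exactly what the change-score test needs at r = 0.5 on the score SD, and also at any r if f is on the change-score SD.

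A reader might also infer that regression to the mean biases the result. It matters conditionally, when the arms happen to differ at t1; it is not a systematic bias.

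Finally, the plan is a two-outcome MANOVA, whereas the power figures above are for one outcome. The joint interaction test is a Hotelling test on two change scores, and its baseline-adjusted counterpart is a MANCOVA. So the figures are not the power of the joint test. They do apply to PMS-B alone, which is the stated primary outcome.

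None of this removes the gain: whichever SD f refers to, adjustment raises power at each r shown.

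**Conclusion.** The concern holds as a weakness of efficiency, not of validity. With equal SDs, the change-score analysis has a variance 2/(1 + r) times that of ANCOVA: 1.54, 1.33 and 1.18 at r = 0.3, 0.5 and 0.7, before the 0.8% finite-sample cost. On the score-SD reading that is worth about 17, 10 and 2 points of power at N = 128; on the change-SD reading about 13, 10 and 6 points.

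The planned test falls below 80% only if f refers to the score SD and, with equal SDs, r is below 0.5. The article states neither, so a shortfall is possible but not shown. The figures rest on 1:1 allocation, equal SDs, no dropout and a single outcome. Because the adjustment costs at most about 0.4% of the standard error and t1 is already collected, the change is worth making without knowing r.

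**What to change.** Name the primary test as an ANCOVA of PMS-B total at t2 on group and PMS-B total at t1, or an equivalent mixed model with the baseline means constrained equal. Use the same form for PMS-C. If a joint test of impairment and coping is to be kept, make it a MANCOVA with both t1 scores as covariates. Report the adjusted mean difference with its 95% confidence interval alongside Hedges' g.

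The cost is analysis wording and one degree of freedom per covariate. It needs no new data, visits or participants. Making PMS-B alone the primary test also sets aside the joint MANOVA as the lead analysis. That goes beyond adding a covariate, but it fits the article's own designation of PMS-B as primary. The change should be fixed before outcome data are compared by group.

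### Follow-up comparisons are tied to the MANOVA's main effects, although the between-group change the plan announces is the group-by-time interaction, which is never named

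*Protocol article*

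**What the plan says.** Three sentences in the protocol article's Statistical analysis section bear on this.

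- The target: "Between-group changes at post-treatment on the impairment and the use of coping strategies will be calculated", using a "2 (pre-treatment/post-treatment) × 2 (experiment group/waiting list) MANOVA".
- The follow-up rule: post hoc "comparisons will be applied if clarification of the main effects of the MANOVA is needed".
- The effect measure: "Effect sizes between the groups will be calculated with Hedges’ g".

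The first hypothesis, at the end of the Background, is also between-group: "we hypothesize that the treatment group receiving the iCBT will show a lower impairment than the wait-list control group". The second is that coping improves relative to the wait-list.

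Under Sample size and power calculations, the total of 128 is derived for a 2 × 2 MANOVA from f = 0.25, α = 0.05 and 80% power. Which effect in that model is powered is not stated. On the pre-post correlation the section says only that "we assumed a conservative retest reliability", without a value. The word interaction does not occur anywhere in the article.

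**The concern.** In a design with two groups measured before and after treatment, the three model terms answer different questions.

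- **Group main effect:** averages the pre-treatment difference, zero in expectation under randomisation, with the post-treatment difference. It therefore estimates half of the treatment effect.
- **Time main effect:** the change averaged over both arms. Natural course or regression to the mean can produce it without any benefit of treatment.
- **Group-by-time interaction:** the difference between arms in change. This is the randomised comparison.

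The follow-up rule names the first two and omits the third. It also has little work to do as written: each factor has two levels, so a significant main effect needs no further comparison to locate it, whereas a significant interaction does call for follow-up. One sentence thus announces a between-group comparison of change, and the next ties follow-up to terms that do not measure it. That leaves a choice among terms open after the data are seen, including a route from a significant time effect to within-arm pre-post tests.

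**Working it through.** **Inputs from the protocol article** (Sample size and power calculations): f = 0.25, which is a standardised difference d = 0.5 for two equal groups; α = 0.05; power 80%; N = 128.

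**Assumptions:** 1:1 allocation, so n = 64 per arm (the ratio is not stated); pre-post correlation r of 0.3, 0.5 or 0.7 (none is given); equal variances at both times; equal baseline means; one outcome, not the joint two-outcome MANOVA.

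**1. The plan's own figure.** For a 1-df F test, the noncentrality is λ = f² × N = 0.0625 × 128 = 8.0. With 126 error df the power is 0.801, so 128 reproduces.

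**2. Does 128 show which term was meant?** For the interaction, λ = (n/2) × d² / [2(1 − r)]. At r = 0.5 this is 32 × 0.25 / 1 = 8.0, again giving 0.801. The stated N therefore fits an interaction test as well as a plain two-group comparison, and it does not show that a main effect was intended.

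**3. The candidate tests at d = 0.5 after treatment, 64 per arm.**

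- Group main effect: λ = (n/2) × (d/2)² / [(1 + r)/2] = 32 × 0.0625 / [(1 + r)/2]
- Interaction: λ = 32 × 0.25 / [2(1 − r)]
- t2 difference adjusted for t1: λ = 32 × 0.25 / (1 − r²), with 125 error df

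| r | Group main effect: λ, power | Interaction: λ, power | Baseline-adjusted: λ, power |
|---|---|---|---|
| 0.3 | 3.08, 0.41 | 5.71, 0.66 | 8.79, 0.84 |
| 0.5 | 2.67, 0.37 | 8.00, 0.80 | 10.67, 0.90 |
| 0.7 | 2.35, 0.33 | 13.33, 0.95 | 15.69, 0.98 |

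The group main effect column only illustrates why that term is a poor guide to efficacy. The plan does not propose it as the efficacy test.

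**4. Time main effect with no treatment effect.** Suppose both arms change by 0.3 SD (an assumed figure). Then λ = 128 × 0.3² / [2(1 − r)] = 11.52 / [2(1 − r)], which is 8.23, 11.52 and 19.20 at r = 0.3, 0.5 and 0.7. The probability of a significant time effect is 0.81, 0.92 and 0.99.

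**The case against.** A reader might infer that the trial will test efficacy on the wrong term. The documents do not support that. The sentence at issue governs optional post hoc comparisons only. The sentence before it sets the target as between-group change, which is the interaction in substance. Both hypotheses and the effect size are between-group, and nowhere is efficacy judged on a main effect or on a within-arm change. A retest reliability that is conservative because it is low would be cautious for the interaction but not for the group main effect, whose power falls as r rises. This also points to the interaction. Main effects may simply be loose wording for the principal MANOVA results. All of this stands.

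It also stands that the size of any regression to the mean in the impairment score is unknown. Eligibility rests on the symptom diary rather than on that score, although t1 is taken within the same two cycles.

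It can further be said that an article may leave the exact model term to an analysis plan that is not shown. That would answer a complaint that the interaction is merely missing. It does not answer this one, because the article does name a term for follow-up, and that term does not match the comparison announced one sentence earlier.

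**Conclusion.** The follow-up rule is inconsistent with the comparison it is meant to clarify and should be fixed. It is a wrongly stated term in a secondary rule and not evidence that the primary test is wrong. The confirmatory test is probably intended to be the group-by-time interaction. The sample size does not change.

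The 33% to 41% power of a group main effect test should not be read as the power of this trial, because no such test is planned. The relevant figures are those for the two tests that do address the randomised effect. Baseline adjustment gains about 18, 10 and 3 percentage points over the interaction at correlations of 0.3, 0.5 and 0.7 (84 − 66, 90 − 80, 98 − 95). These rest on the assumed correlations, 1:1 allocation, d = 0.5 and a single outcome.

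**What to change.** Replace the post hoc sentence in the Statistical analysis section with:

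> Efficacy is judged on the between-group difference at t2 adjusted for the t1 value of the same measure. Follow-up comparisons by outcome are made between groups on this contrast. Main effects of time and group, and within-arm pre-post changes, are not evidence of efficacy.

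If the repeated-measures MANOVA is kept, name the group-by-time interaction as the single efficacy test and tie follow-up to it. Choose one of the two: they address the same effect under randomisation, but they are different tests with different power.

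The cost is one sentence. The t1 measurement is already collected, and neither N nor the assessment schedule changes.
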